**Figure 1 F1:**
[figure not shown]
Selection of personal food stimuli.

#### Set-up call

Within a few days of filling out the online questionnaire, a member of the study team contacts participants to schedule a set-up call via phone or a videoconferencing tool. In this call, the member of the research team explains the procedure of the study. They further help participants install the necessary apps onto their smartphone (m-path KU Leuven, 2022; for EMA and the AAT app (The app can be downloaded on Android devices from this address: https://play.google.com/store/apps/details?id=com.eatlabsbg.eatapp)) and then confirm the correct selection of approach and avoidance foods as determined by the rating task. After the call, participants receive a manual for the study via email, which summarises the study procedures and the use of the smartphone applications and includes participants’ individual three-digit identification code as well as contact information of the study team.

#### Approach-Avoidance Task

We use the smartphone-based AAT as introduced by Zech *et al*.^61^ In this version of the task, participants see stimuli on their horizontally held phone screen and they perform approach or avoidance movements by physically moving the phone towards/away from themselves (see figure 2 and two short introductory videos here: https://osf.io/4k3q9/?view_only=4db6431fd5ee4148a97f3be7f799ea4a). Each trial starts with a fixation dot in the middle of a white screen, which is followed by either one of the food or object stimuli after a 1500 ms delay. While correct approach or avoidance responses make the picture disappear and trigger the start of a new trial, incorrect responses are followed by a 2000 ms display of a black error-cross. If a participant does not respond for 2000 ms, a clock icon is displayed indicating timeout.

**Figure 2 F2:**
[figure not shown]
Illustration of the task. On approach trials, participants move the phone closer to themselves (central image), on avoidance trials, they move it away from themselves (image on the right; adapted from Zech *et al* [61]).

The active and sham AAT trainings feature 4 out of 6 approach-foods, 4 out of 6 avoid-foods, as well as 8 out of 12 control object stimuli. The training sessions consist of four training blocks of 16 trials each, and each training block is preceded by 4 practice trials, yielding a training session of 64 training trials and 16 practice trials, or 80 trials total. The pre-, post- and follow-up bias assessment AATs similarly consist of four blocks preceded each by four practice trials but feature all selected images (6 ‘increase-foods‘, 6 ‘decrease-foods’ and 12 objects). All 24 images are presented one time per block, yielding 96 test trials and 16 practice trials, or 112 trials total. In all AATs, the instructions of the blocks alternate such that participants are instructed to approach foods while avoiding objects in the first block (approach-food blocks) and avoid foods while approaching objects in the second block (avoid-food blocks). This order is the same for all sessions and all participants. Crucially, in the active training AATs, only approach-foods are shown in the approach-food blocks, while only avoid-foods are shown in the avoid-food blocks; sham training instead features both approach-foods and avoid-foods during both approach-food and avoid-food blocks. Completing one session of the AAT/AAI takes about 5 min.

#### Ecological momentary assessment

Participants follow the EMA schedule for a total of 20 days. During the whole period, participants receive two prompts per day (delivered through the smartphone application m-path^69^), one just before the time a participant usually eats lunch and the other in the evening (prompted at an individualised time agreed upon with the participant to represent an end-of-day signal). Table 1 shows the questions that participants answer on those prompts and figure 3 displays the temporal sequence of the study. EMA prompts on days 1–3 of the study only contain the listed questions. On day 4 (the day before the start of the intervention) and day 17 (the day after the end of the intervention), participants receive an instruction to open the AAT application and complete a measurement AAT. On every second day during the intervention phase (days 5 through 16), participants receive an instruction to open the AAT application and complete a training AAT after completing the midday prompt. Thirty minutes after completing the midday prompt, participants receive a notification asking whether they conducted the training. On replying ‘yes’, they receive positive feedback; on replying ‘no’, they are asked to now open the AAT app to conduct the task. The number of sessions was chosen based on earlier, similar studies,^50 52^ balancing participant burden, compliance and intervention intensity.

**Table 1 T1:** Overview of EMA questions (own translations from German)

Item	Midday (all study phases)	Evening Days 1–4 and 17–20	Evening Days 5–16	Evening: follow-up
When was the last time you ate something?	X			
What type of meal was it? (breakfast, lunch, dinner, snack)	X			
How hungry are you right now?	X	X	X	
Do you feel like you have everything under control?	X			
Do you feel like you are on top of things?	X			
How optimistic do you feel right now?	X			X
How happy do you feel right now?	X			X
How lonely do you feel right now?	X			X
How depressed do you feel right now?	X			X
How angry do you feel right now?	X			X
How mad do you feel right now?	X			X
How tense do you feel right now?	X			X
How anxious do you feel right now?	X			X
How much do you want to stick to your dietary goals *for the rest of the day*?	X			
How much do you want to stick to your dietary goals *tomorrow*?		X		X
How strong has your craving for this food been *today*?*		X		X
How much of this food have you eaten *today*?*		X		X
Have you said things today without thinking?	X	X	X	X
Have you spent more money today than you wanted to?	X	X	X	X
Have you felt impatient today?	X	X	X	X
Have you made a spontaneous decision today?	X	X	X	X
How strong has your craving for this food been *since the midday questionnaire*?*			X	
How much of this food have you eaten *since the midday questionnaire*?*			X	
How much do you expect that this task will help you reach your dietary goals?†	X†			
Throughout the whole study, how often did you push this food away from yourself?*				X
Please indicate the day your last period started.				X

All items are answered on a slider from 0 to 100 unless indicated differently in parentheses. Midday prompts remain the same across the entire study duration. Evening prompts differ depending on the study phase as indicated:.

*These items are asked alongside a food image and are repeated for each image (six ‘increase-food‘ and six ‘decrease-food’ images).

†This item is only asked after the first and the last AAT session (days 5 and 15).

AAT, Approach Avoidance Task; EMA, ecological momentary assessment.

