#### Procedure

The procedure for study participation is as follows: after interested participants contact the study team, they receive an individual participant code and a web link to the baseline questionnaire. At this point, an R-script (The function *sample* randomly outputs the number ‘1’ or ‘2’ which correspond to the conditions.) randomises participants to either the intervention or control group with the condition unknown to the study team. After a set-up call with a member of the research team within a few days of filling out the questionnaires, participants start receiving EMA prompts and AAT as described above. Figure 3 shows the timeline of the whole study. Throughout the study period, participants can contact study personnel who also monitor compliance to the EMA and AAT schedule and contact participants in case of low compliance: participants receive an email if they miss more than one of the first three AAT/AAI sessions.

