### Outcomes

#### Main outcomes

This study uses three main outcome measures. The first outcome measure is participants’ self-reported intake of ‘increase’ and ‘decrease’ foods according to the EMA schedule outlined above, on a slider from 0 (labelled ‘nothing’) to 100 (‘very much’). The second outcome measure is participants’ self-reported craving for those same foods in the same manner. Simple, single-item measures reduce participant burden but might negatively affect reliability. To ameliorate this, measures are applied for each food separately. Time trends that might indicate changes in participants’ perceptions of amounts as ‘much’ or ‘little’ will be checked in the control group and, if present, controlled for in analyses.

The third outcome measure is the approach bias for all selected foods based on the RT and force in the AAT. The RT is defined as the time from picture onset to movement onset. Force is defined as the peak acceleration in the correct direction during a trial, standardised within participant by dividing every individual’s measurement of force by the participant-specific SD. Separately for approach and avoidance trials as well as for sessions, the RT and the force will be averaged across the four AAT blocks for each specific food stimulus. For objects, we will also average across the different stimuli. The average approach or avoid response for objects on a session will be subtracted from stimulus-specific food approach or avoidance response on that session to achieve food-specific *single-difference* approach and avoidance scores according to these formulas:

Stimulus−specificavoidance=[food−specificavoidance]−[averageobjectavoidance]

Stimulus−specificapproach=[food−specificapproach]−[averageobjectapproach]

*Double-difference scores* will be used as a full bias score per food stimulus and session, according to the formula: ((food-specific avoidance)−(food-specific approach))−((average object avoidance)−(average object approach)).

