#### Overall intervention effectiveness

The first set of research questions relates to the effectiveness of the intervention as compared with the control condition from pretraining to post-training. To this end, we use multilevel models to predict intake of trained ‘increase’ and ‘decrease’ foods as a function of timepoint (3 days preintervention vs postintervention), condition (intervention vs control) and their interaction. Equivalent models test the intervention effect on approach biases towards—and craving for—the two food categories. To test to what degree the effect of the training intervention is specific to trained foods, we then use data from trained and untrained stimuli and add a variable that indicates whether a food appeared in the training or not (trained vs untrained) and all interaction terms to the model. This is followed up with tests to determine whether changes in the approach bias are mainly driven by changes in approach—or avoidance RTs. We further test the moderating role of intentions, baseline stimulus craving and person-level variables obtained from the questionnaires, as well as contingency awareness and expectancy by adding the relevant variable and its interaction terms to the equations. Finally, we examine the mediating effect of craving for changes in intake.

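### The pre and post evening windows lie 16 days apart, so their weekend content usually differs within a participant; this adds some avoidable noise to change in intake and craving, without biasing the arm comparison

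*Protocol article*

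**What the plan says.** The section on ecological momentary assessment states: "Participants follow the EMA schedule for a total of 20 days". Table 1 places the whole-day food items, such as "How much of this food have you eaten *today", on "Evening Days 1–4 and 17–20". The intervention phase between these windows lasts 12 days (days 5 to 16).

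Under Procedure, prompting begins "After a set-up call with a member of the research team within a few days of filling out the questionnaires". No weekday for day 1 is named there or in the section on the set-up call.

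Under Overall intervention effectiveness, intake is modelled on "timepoint (3 days preintervention vs postintervention), condition (intervention vs control) and their interaction", with equivalent models for craving and approach bias. The article does not say which three of the four collected days are meant, and it refers to a preregistration, not shown, for the exact model formulas.

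Under Main outcomes, the article adds: "Time trends that might indicate changes in participants’ perceptions of amounts as ‘much’ or ‘little’ will be checked in the control group". Any trend found is then to be controlled for.

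**The concern.** Two of the three main outcomes, intake and craving, are daily self-reports that may differ between weekends and weekdays. If so, a participant whose pre window has no weekend day and whose post window has two will show a change unrelated to training. Another participant, starting on a different weekday, will show the reverse. Windows a whole number of weeks apart would have avoided this for everyone.

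Two things are at stake. One is precision: weekday composition becomes a source of between-person variance in the pre-post change. The other is how a control-group time trend is read. The plan links such a trend to changed perception of what counts as much or little, while an uneven weekday mix could produce one too.

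**Working it through.** **Inputs.** From the article: windows on days 1–4 and 17–20, three days per window in the effectiveness model, no fixed start weekday, two arms randomised individually on the same schedule, N = 150. Not in the documents and therefore assumed: the weekend-weekday difference w (5 to 10 points on the 0–100 slider), the SD of a person's pre-post change (15 points) and the distribution of start weekdays.

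**The plan's own figure.** The plan gives no figure on this point. Its power statement (0.80 at g = 0.50 and about 0.88 at g = 0.56, for approach bias) is used below only as a scale, and it is consistent with itself: (1.960 + 0.842) × 0.56/0.50 − 1.960 = 1.178, and Φ(1.178) = 0.88.

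**Step 1: offset.** 17 − 1 = 16 days = 2 × 7 + 2, so every day of the post window falls two weekdays later than its counterpart.

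**Step 2: weekend days (Saturday and Sunday) in the four-day windows.**

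| Start | Days 1–4 | Days 17–20 | Difference |
|---|---|---|---|
| Mon | 0 | 1 | +1 |
| Tue | 0 | 2 | +2 |
| Wed | 1 | 2 | +1 |
| Thu | 2 | 2 | 0 |
| Fri | 2 | 1 | −1 |
| Sat | 2 | 0 | −2 |
| Sun | 1 | 0 | −1 |

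Six of seven differ. The differences sum to zero.

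**Step 3: three-day windows.** Let d be the difference in weekend days and k = 3 the window length. With evenly spread starts the mean of d is zero, so the added change-score SD is w × √(mean of d²)/k. With Monday–Friday starts only, the shift is w × (mean of d over those five starts)/k.

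| Pre vs post days | d for Mon … Sun starts | Starts that differ | Added SD | Shift, Mon–Fri starts |
|---|---|---|---|---|
| 1–3 vs 17–19 | 0, 1, 2, 1, −1, −2, −1 | 6 of 7 | √(12/7)/3 = 0.44w | 0.6/3 = 0.20w |
| 1–3 vs 18–20 | 1, 2, 2, 0, −2, −2, −1 | 6 of 7 | √(18/7)/3 = 0.53w | 0.6/3 = 0.20w |
| 2–4 vs 17–19 | 0, 1, 1, 0, −1, −1, 0 | 4 of 7 | √(4/7)/3 = 0.25w | 0.2/3 = 0.07w |
| 2–4 vs 18–20 | 1, 2, 1, −1, −2, −1, 0 | 6 of 7 | √(12/7)/3 = 0.44w | 0.2/3 = 0.07w |

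Every row sums to zero. For comparison, the four-day windows give √(12/7)/4 = 0.33w and 0.6/4 = 0.15w.

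**Step 4: size in variance and power.** Relative to a change variance of 15² = 225:

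- Smallest case: (4/7)/9 × 5² = 1.6, and 1.6/225 = 0.7%.
- Largest case: (18/7)/9 × 10² = 28.6, and 28.6/225 = 12.7%.

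Against a notional power of 0.80, Φ(2.802/√1.007 − 1.960) = 0.797 and Φ(2.802/√1.127 − 1.960) = 0.75. The plan states no power for intake or craving, so these show scale only.

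**Step 5: bias and trend.** A simulation used the four-day windows, N = 150, simple randomisation, no treatment effect, an assumed weekend effect of 0.5 change SD and 20,000 runs.

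| Start days | Mean time effect (SD) | Condition-by-time contrast | Type I error of that contrast | Control-group trend test rejects |
|---|---|---|---|---|
| Even over the week | about 0 | about 0 | 0.049 | 4.8% |
| Mon–Fri | +0.076 | about 0 | 0.052 | 10.0% |
| Tue–Sat | about 0 | about 0 | 0.050 | 5.1% |

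**The case against.** The strongest reply is that the trial's question is untouched. Both arms follow the same schedule and are randomised individually, so any shift from weekday composition goes into the timepoint term and drops out of the interaction. This stands in full. It also covers the trend adjustment: removing a trend common to both arms does not depend on what caused it, so a wrong explanation of that trend would not alter the arm comparison.

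A reader might infer from the weekday counts that the schedule builds a false time trend into intake and craving. The document does not support that. The differences cancel over evenly spread starts, and a net shift needs clustering, about which the article says nothing. Monday–Friday set-up calls would not settle it either: if day 1 is the day after the call, starts run Tuesday to Saturday and the mean difference for the four-day windows is exactly zero.

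A third reply is that w is unknown and need not be one number. Foods are chosen individually, and increase-foods and decrease-foods could have weekend effects of opposite sign. This is fair, and it is why the size is given as a multiple of w.

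Finally, the preregistration may already contain a day-type term. That also stands, so the absence of such a term from a condensed article is not itself the point. The point rests on the schedule, which the article does fix.

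**Conclusion.** The point holds as a minor one about precision. The spacing of the windows makes weekend content differ between pre and post for most start weekdays: six of seven over four days, and six or four of seven over three. If intake or craving differs at weekends, this adds a change-score SD of about 0.25w to 0.53w over the plausible three-day windows. That is about 1–13% of the variance under the assumed w of 5–10 points, an assumed change SD of 15 and evenly spread starts. With a small w the loss is negligible.

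The condition-by-time effect is not biased. A net time trend arises only if start days cluster. With Monday–Friday starts it would be about 0.07w to 0.20w in each arm, or 0.3 to 2.0 points for the assumed w. In that case the control-group check could attribute a weekday effect to changed perception of amounts. This would affect how the trend or a within-arm change is described, not the estimated intervention effect.

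**What to change.** Unless the preregistered formulas already contain it, add a weekend/weekday indicator for each EMA day to the pre-post models for intake and craving, and to the control-group time-trend check. Where increase-foods and decrease-foods share a model, let the indicator's effect differ between them. The indicator comes from prompt dates that the EMA system should already hold, works for any choice of three days, and costs one or two coefficients per model. It removes the average weekend effect; person-specific departures from that average would remain as noise.

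No change to the schedule is needed. Fixing day 1 on a Thursday may look attractive because it balances days 1–4 against 17–20, but it is not advised. Days 1–3 vs 17–19 would then hold one weekend day against two, and days 2–4 vs 18–20 two against one. Day 20, and so the follow-up four weeks later, would fall on a Tuesday for every such participant.

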**Figure 3 F3:**
[figure not shown]
Time schedule of the whole study period. AAI, approach-avoidance intervention; AAT, Approach Avoidance Task; EMA, ecological momentary assessment.

In addition, on day 6 and day 16 (the first day and the last day including an AAT/AAI session), participants further indicate their expectancy of how much the task will help them reach their dietary goals. Four weeks after the end of the initial 20-day EMA period, participants receive one additional EMA questionnaire and a measurement AAT in the evening. After performing this final AAT, participants indicate how often they believed they pushed or pulled each of their ‘decrease-foods’ and ‘increase-foods’.

#### Procedure

The procedure for study participation is as follows: after interested participants contact the study team, they receive an individual participant code and a web link to the baseline questionnaire. At this point, an R-script (The function *sample* randomly outputs the number ‘1’ or ‘2’ which correspond to the conditions.) randomises participants to either the intervention or control group with the condition unknown to the study team. After a set-up call with a member of the research team within a few days of filling out the questionnaires, participants start receiving EMA prompts and AAT as described above. Figure 3 shows the timeline of the whole study. Throughout the study period, participants can contact study personnel who also monitor compliance to the EMA and AAT schedule and contact participants in case of low compliance: participants receive an email if they miss more than one of the first three AAT/AAI sessions.

### Outcomes

#### Main outcomes

This study uses three main outcome measures. The first outcome measure is participants’ self-reported intake of ‘increase’ and ‘decrease’ foods according to the EMA schedule outlined above, on a slider from 0 (labelled ‘nothing’) to 100 (‘very much’). The second outcome measure is participants’ self-reported craving for those same foods in the same manner. Simple, single-item measures reduce participant burden but might negatively affect reliability. To ameliorate this, measures are applied for each food separately. Time trends that might indicate changes in participants’ perceptions of amounts as ‘much’ or ‘little’ will be checked in the control group and, if present, controlled for in analyses.

The third outcome measure is the approach bias for all selected foods based on the RT and force in the AAT. The RT is defined as the time from picture onset to movement onset. Force is defined as the peak acceleration in the correct direction during a trial, standardised within participant by dividing every individual’s measurement of force by the participant-specific SD. Separately for approach and avoidance trials as well as for sessions, the RT and the force will be averaged across the four AAT blocks for each specific food stimulus. For objects, we will also average across the different stimuli. The average approach or avoid response for objects on a session will be subtracted from stimulus-specific food approach or avoidance response on that session to achieve food-specific *single-difference* approach and avoidance scores according to these formulas:

Stimulus−specificavoidance=[food−specificavoidance]−[averageobjectavoidance]

Stimulus−specificapproach=[food−specificapproach]−[averageobjectapproach]

*Double-difference scores* will be used as a full bias score per food stimulus and session, according to the formula: ((food-specific avoidance)−(food-specific approach))−((average object avoidance)−(average object approach)).

#### Secondary outcomes

Dietary intentions are measured according to the outlined EMA schedule.

### Data analysis plan

Data analysis will serve to investigate a series of research questions relating to different aspects of the study. In this section we will provide a brief description. Full details on the data analysis, including the exact multilevel analysis formulas, are available in the preregistration at https://osf.io/yn7kt.

#### Data exclusion

For analyses regarding the effectiveness of the AAI, we exclude participants who did not conduct any of the AATs during the intervention phase, as we regard them as ‘not treated’. For the remaining participants, sensitivity analyses are performed to test whether the number of completed training sessions affects intervention effectiveness. For analyses of approach bias, we exclude error trials and trials with RTs that deviate more than ±3 SD from the individual mean of the participant in that AAT session. If more than 25% of trials must be excluded based on these criteria, the whole AAT session is excluded from further analysis. This post hoc session exclusion does not affect whether a participant is counted as ‘not treated’ or not in the analyses regarding the effectiveness of the AAI.

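### The ±3 SD reaction-time rule has no absolute floor, so with a moderate or large within-session SD it often keeps anticipatory responses, which add noise to the approach-bias outcome

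*Protocol article*

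**What the plan says.** The Data exclusion section sets two trial-level criteria: "we exclude error trials and trials with RTs that deviate more than ±3 SD from the individual mean of the participant in that AAT session". A session-level rule builds on them: "If more than 25% of trials must be excluded based on these criteria, the whole AAT session is excluded from further analysis". No absolute lower RT limit is named, and timeouts are not mentioned.

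Other sections bear on how this works:

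- Main outcomes: "The RT is defined as the time from picture onset to movement onset". For the bias score, "the RT and the force will be averaged across the four AAT blocks for each specific food stimulus".
- Approach-Avoidance Task: "incorrect responses are followed by a 2000 ms display of a black error-cross". Separately, "If a participant does not respond for 2000 ms, a clock icon is displayed indicating timeout".
- Approach-Avoidance Task, text after Figure 2, on the measurement sessions: "All 24 images are presented one time per block, yielding 96 test trials and 16 practice trials". The blocks alternate: "participants are instructed to approach foods while avoiding objects in the first block (approach-food blocks) and avoid foods while approaching objects in the second block".

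The article reports no RT mean or SD. The Data analysis plan refers to a preregistration for full details, which is not at hand.

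**The concern.** A two-sided SD rule should catch responses that are too fast to be reactions to the picture as well as those that are too slow. RTs cannot fall below zero and usually have a long right tail. That tail widens the SD and pushes the lower limit down into the range where anticipations lie. The anticipations widen the SD further and so help to hide themselves.

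Such responses are plausible in this task, because the picture follows the fixation dot after a stated 1500 ms delay. Those in the wrong direction are dropped as errors. Those in the correct direction can stay.

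Approach bias is one of three main outcomes. The sample size was worked out on it, and the control-group state and trait analyses use it. Its food-level scores rest on very few trials, so one invalid RT carries much weight.

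**Working it through.** **Inputs from the article.** 24 images × 4 blocks = 96 test trials. Foods are approached in two blocks and avoided in two, so each food has 2 approach and 2 avoidance trials per measurement session.

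**Inputs assumed, because the article gives none.** RT mean 600–800 ms, within-session SD 100–260 ms, anticipations at 50–200 ms, and half of anticipations in the correct direction.

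**1. Where the lower limit falls.** Limit = mean − 3 × SD.

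- It exceeds 200 ms only if SD < (mean − 200)/3. That is 133 ms at mean 600, 150 at 650, 167 at 700, 183 at 750 and 200 at 800.
- It reaches zero only if SD ≥ mean/3. That is 200 ms at mean 600, 233 at 700 and 267 at 800.
- Examples at mean 700: SD 100 gives 400 ms, SD 150 gives 250 ms, SD 200 gives 100 ms, SD 250 gives −50 ms.

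**2. Share of anticipations removed.** Simulated sessions of 96 trials with shifted-lognormal RTs cut at 2000 ms and 3,000 sessions per setting. All anticipations counted here are in the correct direction and enter the mean and SD.

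| Mean, SD (ms) | 1 per session | 5 per session | 10 per session |
|---|---|---|---|
| 700, 100 | 100% | 92% | 1% |
| 700, 150 | 95% | 24% | 0% |
| 700, 200 | 24% | 0.2% | 0% |
| 700, 250 | 0.6% | 0% | 0% |
| 600, 150 | 52% | 4% | 0% |
| 800, 200 | 73% | 4% | 0% |

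Reading down the table, a larger SD defeats the rule. Reading across, several anticipations defeat it even at SD 100.

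**3. Weight of one kept trial.** Take 125 ms against a typical 700 ms. The cell mean shifts by (700 − 125)/2 = 287.5 ms, and that food's double-difference score by about the same amount. Averaged over the four trained foods of a category, this is 287.5/4 ≈ 72 ms for that person in that session.

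**4. Effect on the session-level bias score.** The ±3 SD rule alone was compared with a 200 ms floor followed by ±3 SD, for means of 600–750 ms, SDs of 100–260 ms and 1–5% anticipations. The floor lowers the sampling variance of the score by about 2–18%. Without it the variance is higher by a factor of 1/0.98 = 1.02 to 1/0.82 = 1.22, or roughly 2–20% more. The exact figures depend on the RT shape assumed.

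**5. The 25% session limit.** By Chebyshev's inequality at most 1/9 of trials can lie beyond 3 SD: 96/9 = 10.7, so at most 10. Exclusion needs more than 24 trials. RT outliers alone can never trigger it, and at least 25 − 10 = 15 error trials are needed. Whether timeouts count therefore matters. As an illustration, 24 timeouts and 6 errors are 30/96 = 31% of trials lost. If timeouts do not count, the tally is 6/96 = 6% and the session stays.

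**The case against.** The strongest reply is that the article summarises an analysis whose details are in a preregistration, and an RT floor or the coding of timeouts could well be there. That stands as a caution. But the Data exclusion section states a rule that reads as complete and ties session exclusion to it, so how that stated rule performs is open to comment.

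Second, how often anticipations occur, and how large the SD is, are both assumed. This also stands, and it makes the conclusion conditional.

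Third, a per-session ±3 SD rule is prespecified, reproducible and a recognised convention. That is true, but the convention is weak where the cells hold two trials.

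Three stronger readings are tempting, and the document does not support them:

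- A reader might infer that the rule cannot remove anticipations, or that its limit lies at or below zero. Both depend on the SD. With SD 100–150 ms and a single anticipation per session, the table shows removal of 52–100%.
- A reader might infer that timeouts contaminate the bias score. RT runs to movement onset, so a timeout without movement has no RT and cannot enter a mean. Only the session count is in question. Even there, the article describes different on-screen feedback and does not say whether error trials include timeouts. It is ambiguous, not wrong.
- A reader might set the 287.5 ms shift against the shifts of 64 to 244 in the power analysis under Participants. Those are changes in a group mean, whereas 287.5 ms concerns one food, one session and one person. The power analysis also resampled real data, so some of this noise may already be in the 150 participants. A loss against planned power is not shown.

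**Conclusion.** The point holds in a conditional form. As stated, the rule often fails to remove correct-direction anticipations once the SD reaches about 170 ms at means of 650–750 ms, or when several occur in a session. With a smaller SD and few anticipations it works for the most part.

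The cost is modest: roughly 2–20% more measurement-error variance in the RT-based bias score if 1–5% of trials are anticipations. The effect on the condition-by-time estimate should be smaller in proportion, because that estimate also carries participant and stimulus variation. The rule is the same in both arms, so no directional bias follows. Self-reported intake and craving are untouched.

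The conclusion rests on assumed RT means, SDs and anticipation rates, and on the preregistration not already setting a floor. The status of timeouts needs a clarification only.

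**What to change.** Before unblinding, amend the Data exclusion rule and the matching analysis code:

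1. Exclude RTs below a fixed absolute floor (for example 200 ms) before computing the participant-session mean and SD.
2. Apply ±3 SD to the remaining correct trials, identically in both arms and all sessions.
3. Count sub-floor trials towards the 25% session limit, and state that timeouts count too.

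If the preregistration already contains a floor, bring the article's wording into line with it.

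The cost is a few lines of text and code and no new data. A very small share of valid trials is lost, well under 1% in the simulations, mostly slow ones beyond an upper limit that tightens once the SD is no longer inflated. Occasionally a further session will be dropped.
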